### Sample size and statistical power

The sample size was calculated based on the occurrence of MAKE30 on septic patients, which was around 35% [17]. With a noninferiority limit of 1.5%, a total of 312 study participants (156 in each group) would result in a power of at least 80% with a one-sided type-1 error rate (*α*) of 2.5%, allowing a 20% withdrawal rate in each group.

### Statistical analysis

Measurement data that conform to normal distribution will be described as mean ± SD, while ones that do not will be reported as the median and interquartile range (IQR). Count data will be notified as frequencies and proportions. As for single-factor analysis, the difference of measurement data will be compared with *T* test between two groups or with one-way analysis of variance among three groups. Chi-square test and Fisher’s exact test will be used for rate comparison. As for multi-factor analysis, variables which showed a significant difference in the univariate analysis will be processed by logistic multivariate regression analysis. Multiple linear regression analysis will be used to demonstrate the linear relationship between variables. *P* value < 0.05 will be considered statistically significant. SPSS 24.0 will be used to complete data processing and statistical analysis.

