### Study outcomes

The primary outcome is MAKE28 (major adverse kidney events) [22]—a composite of in-hospital death, new renal replacement therapy, or persistent renal dysfunction (defined by an estimate glomerular filtration rate (eGFR) lower than 60 ml/min/1.73 m^2^ for at least 3 months [23, 24]) within 28 observational days.

Secondary outcomes will include:
The occurance of AKI which is diagnosed according to the Kidney Disease Improving Global Outcomes (KDIGO) criteria [25];Twenty-eight day mortality;Electrolyte disturbance, including hypernatremia, hyperchloremia, and hyperkalemia as well as hyponatremia, hypochloremia, and hypokalemia;Changes of renal functions based on the biomarkers measured from the participants’ plasma and urine samples collected in the first 3 days after enrolment; andOther clinical outcomes: ICU stay days, ventilator days, vasopressor days, and RRT days.

Pre-specified subgroups for primary and secondary outcome analyses will mainly include:
With or without acute kidney injury (no AKI, AKI stage 1, AKI stage 2, or AKI stage 3);With or without septic shock;Low versus high severity of sepsis: mild, moderate, and severe (classified by SOFA scores or Acute Physiology and Chronic Health Evaluation II (APACHE II) scores); andIntravenous infused volumes of the assigned crystalloids.

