### Primary analysis

The primary analysis will be an intention-to-treat comparison of the primary outcome of MAKE28 between the saline and acetate Ringer’s solution. A generalized linear mixed-effects model will be used including fixed effects (sex, age, body mass index, group assignment, principal diagnosis, crystalloids received prior to ICU, SOFA score, APACHE II score, mechanical ventilation status, vasopressor usage, etc.) and random effects. It is aimed to describe patients’ baseline characteristics and eliminate confounding factors.

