### Additional secondary analysis

Statistical methods mentioned in the statistical analysis will be applied according to the characteristics and distribution of the data.
Compare the secondary outcome between the two groups;Subgroup analysis will include:
Septic shock (yes/no)Stage of AKI on the enrolment day (no AKI, AKI, chronic kidney disease without receiving RRT regularly)intravenous volumes of the assigned crystalloidsThe APACHE II scores and SOFA scores at the day of enrolmentReceipt of mechanical ventilation (yes/no) and ventilation daysReceipt of vasopressor (yes/no), vasopressor category, and max dosesReceipt of RRT (yes/no) and RRT daysMain diagnosis at the time of admission to hospital (nervou s system disease, respiratory system disease, cardiovascular system disease, digestive system disease, urinary system disease, hematologic system disease, endocrine system disease)Complications (hypertension, diabetes, coronary heart disease, etc.)

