### Data collection and management

Patients’ demographic data, main diagnosis, comorbidities, assigned crystalloids, general vital signs, SOFA scores, APACHE II, infection indices, and indices of multi-organ function including renal function, respiratory function, cardiac function, etc. at the time of enrolment will be collected as baseline data. Clinical information including infection indices (white blood cell count, procalcitonin, etc.), organ function indices (renal function (creatinine, urea nitrogen, cystatin C, urine volumes, etc.), respiratory function (PO_2_/FiO_2_, ventilation situation, etc.), hepatic function (total bilirubin, etc.), and indices of internal environment (blood gas analysis) will be detected during the first 5 days in ICU, and treatments such as vasopressors, mechanical ventilation, RRT, and electrolyte supplement will be recorded. These data and infused volumes of the assigned fluids will be collected for at least 5 days or until ICU discharge. ICU stay days, vasopressor days, RRT days, and ventilation days will be counted during 28 days after enrolment. These data will be collected to assess and analyze primary and secondary outcomes. Besides, patients’ blood and urine samples within the first 3 days after enrolment will be collected and stored for testing possible biomarkers for identifying AKI at an early stage.

Patients’ information and clinical data will be collected from the Hospital Information System (HIS) of the hospitals involved in this study and recorded in the Case Report Format (CRF) by the trial manager or trained personnel. An electronic password-protected excel, which will be applied for statistical analysis, will be created to summarize the data of all participants. All the data will be accessed by only investigators and authorized personnel to monitor the completeness and authenticity of the table. The confidentiality is secured and all the data will be preserved for the purpose of a secondary analysis or investigations by the investigators. To protect patients’ privacy, their names will not appear on the CRF table. Every participant will only be recognized by their study ID.

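### The only two-group test named for continuous data is an unadjusted t test, so the change-in-renal-function outcome loses precision that the enrolment renal function already collected could recover

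*Protocol article*

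**What the plan says.** Study outcomes lists this secondary outcome: "Changes of renal functions based on the biomarkers measured from the participants’ plasma and urine samples collected in the first 3 days after enrolment". It does not state a reference value, a time point, or whether the analysed quantity is a difference or a follow-up level.

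Additional secondary analysis asks the analyst to "Compare the secondary outcome between the two groups" and gives the method by reference: "Statistical methods mentioned in the statistical analysis will be applied according to the characteristics and distribution of the data". The section referred to, Statistical analysis, offers three things that could bear on a continuous outcome:

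- Under single-factor analysis: "the difference of measurement data will be compared with *T* test between two groups or with one-way analysis of variance among three groups".
- Under multi-factor analysis: "variables which showed a significant difference in the univariate analysis will be processed by logistic multivariate regression analysis".
- A sentence on linear models: "Multiple linear regression analysis will be used to demonstrate the linear relationship between variables".

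Primary analysis does specify an adjusted comparison of the fluids ("A generalized linear mixed-effects model will be used including fixed effects"), but for MAKE28 only. Its covariate list is open-ended and does not name baseline renal function.

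On the data available, Data collection and management says that "indices of multi-organ function including renal function, respiratory function, cardiac function, etc. at the time of enrolment will be collected as baseline data".

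**The concern.** A renal marker measured a day or two after enrolment depends heavily on its level at enrolment. The trial admits patients from no AKI to AKI stage 3, so that level will vary widely, and Main secondary analysis itself expects initial renal function to matter for outcome. A test that takes no covariate leaves this variation in the error term.

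Two things are at stake. The first is precision: the confidence interval for an early renal effect is wider than the collected data require. The second is the reading of the result if the arms differ at enrolment. Parallel control and allocation assigns acetate Ringer's solution in odd months and saline in even months at both centres, and the trial is open-label. Clinicians can foresee the fluid, and case mix may differ by month. A baseline difference is therefore a more realistic worry than under concealed patient-by-patient randomisation, and the t test has no means of allowing for it.

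**Working it through.** **Which test applies.** The multi-factor rule is logistic and picks covariates by univariate significance, so it is not a baseline adjustment of a continuous outcome. The linear regression sentence is not tied to the fluid comparison, to this outcome or to a baseline value. The mixed model belongs to MAKE28. That leaves the t test as the only named comparison of two groups on continuous data.

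**Inputs.** The plan gives no power or precision figure for this outcome, so there is none to reproduce. The sample size statement (312) concerns MAKE28 and is used here only for patient numbers: 156 per arm, or 156 × 0.8 ≈ 125 after the 20% withdrawal allowance. The test is at 5%, taken as two-sided. *Assumed*: correlation rho between enrolment and follow-up values (the documents give none, so 0.3 to 0.9 is shown), the same SD σ at both times, and independent patients.

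**Variance per patient.**

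- t test on follow-up value: σ²
- t test on change: 2σ²(1−rho)
- Adjusted for enrolment value: σ²(1−rho²)

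Adjusted relative to change: (1−rho²)/[2(1−rho)] = (1+rho)/2. Adjusted relative to follow-up: 1−rho². Both ratios are below 1 for any rho between 0 and 1.

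**Power of the adjusted analysis for an effect that gives the t test 80%.** The effect is then 2.8016 standard errors of the t test, so adjusted power ≈ Φ(2.8016/√ratio − 1.96). For rho 0.5: 2.8016/√0.75 − 1.96 = 1.275, giving 89.9%. Results are the same for 125 and 156 per arm:

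| rho | Ratio to change | Power if change test has 80% | Ratio to follow-up | Power if follow-up test has 80% |
|---|---|---|---|---|
| 0.3 | 0.65 | 93.5% | 0.91 | 83.6% |
| 0.5 | 0.75 | 89.9% | 0.75 | 89.9% |
| 0.7 | 0.85 | 86.0% | 0.51 | 97.5% |
| 0.9 | 0.95 | 82.0% | 0.19 | about 100% |

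At rho 0.5 with 125 per arm, the effect detectable with 80% power is 2.8016 × √(2/125) = 0.354 SD by either t test, and 0.354 × √0.75 = 0.307 SD with adjustment.

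**Baseline imbalance.** If the arms differ at enrolment by d, the expected error is −(1−rho)d for the change score and +rho·d for the follow-up value. One standard error of the baseline difference at 125 per arm is √(2/125) = 0.126 SD. At rho 0.5 that gives errors of −0.063 and +0.063 SD.

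A simulation of 20,000 individually randomised trials with no fluid effect (125 per arm) separates the average from the conditional behaviour:

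- Over all trials the mean error was at most 0.0015 SD in absolute size, and type I error of the two t tests was 4.7% to 4.9%.
- Among trials with a baseline difference above 1 standard error, at rho 0.5, the change score was off by −0.095 SD (type I error 8.3%) and the follow-up value by +0.098 SD (9.2%).
- In the same subset at rho 0.7, the figures were −0.057 SD (7.1%) and +0.135 SD (12.0%).
- The adjusted estimate had a mean error of about zero throughout.

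**The case against.** The strongest reply is that the t test is not assigned to this outcome in so many words. The methods are to be matched to the data, linear regression is on the list, and a full protocol or SAP may name a model. It is true that the link is by general reference and so an inference. But the article does state how two groups are compared on continuous data, and nothing it says ties regression to that comparison. The point concerns a stated method, not an omitted detail.

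A reader might infer that the plan commits to a change score in which baseline enters by subtraction. It does not: the outcome is worded as a change, but no estimator is defined. That is why both readings are worked through above.

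A reader might also infer that chance differences between fluid months bias the result. Under randomisation they do not, as the simulation's overall means show; the error is conditional on an imbalance having occurred. Systematic differences between months are a separate possibility that the documents neither establish nor exclude, and baseline adjustment would not be guaranteed to remove them.

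Three further objections stand in part:

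- Renal status is not ignored. Subgroups by AKI stage are prespecified for primary and secondary outcomes. Subgrouping does not adjust the overall comparison, however.
- The outcome rests on plasma and urine samples from the first 3 days, and the article does not say that each stored-sample biomarker has a value from before study fluid. A sample drawn after the fluid has started is not a valid baseline.
- The gain against a change score is small if rho is high, and the power figures treat patients as independent although fluid is allocated by month. They show relative efficiency and do not predict this trial's power.

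**Conclusion.** The point holds as one of precision. As written, the plan leads to an unadjusted comparison of a continuous renal outcome although enrolment renal function is collected. Relative to adjustment, the change-score variance is larger by a factor of 2/(1+rho): 54% larger at rho 0.3, 33% at 0.5, 18% at 0.7 and 5% at 0.9. Against a follow-up t test the loss runs the other way and grows with rho. These sizes rest on an assumed rho, equal SDs at the two times and independent patients.

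The documents do not support calling the t test biased on average. What can be said is that its estimate moves with whatever baseline difference is observed, and that a foreseeable odd/even-month, open-label schedule gives more reason to guard against such a difference.

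The consequence is confined to a secondary outcome. The MAKE28 analysis and the sample size are untouched. The change is worth making, but it is not critical.

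**What to change.** In Statistical analysis and Additional secondary analysis, state that the fluids are compared on each continuous renal measure by linear regression, or a linear mixed model, of the follow-up value on fluid group and the enrolment value of the same measure. This covers creatinine, urea nitrogen and cystatin C, and the stored-sample biomarkers only where a sample was taken before study fluid. Use a log scale where the measure is skewed. Report the adjusted difference, or ratio, with its confidence interval in place of the t test.

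Name centre and month in the model explicitly. They cannot be borrowed from the MAKE28 model, because Primary analysis lists neither and leaves its random effects unspecified. Since the assigned fluid is constant within a month of enrolment, month should enter as a random effect; a separate fixed term for every month would absorb the fluid contrast.

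The cost is analysis wording, with no new data for the routine measures if each was recorded at enrolment, and the planned software can fit the model. The drawback is that patients without an enrolment value need a stated handling rule, which a change score would need as well.

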### Analytic rationale

This study will recruit participants with a wide range of baseline risk factors of the primary outcome who are exposed to the study intervention and can be divided into subgroups of distinct renal function or received crystalloid volumes. The baseline and secondary analysis will figure out whether the intervention makes a difference to patients’ prognosis.

### Primary analysis

The primary analysis will be an intention-to-treat comparison of the primary outcome of MAKE28 between the saline and acetate Ringer’s solution. A generalized linear mixed-effects model will be used including fixed effects (sex, age, body mass index, group assignment, principal diagnosis, crystalloids received prior to ICU, SOFA score, APACHE II score, mechanical ventilation status, vasopressor usage, etc.) and random effects. It is aimed to describe patients’ baseline characteristics and eliminate confounding factors.

### Main secondary analysis

We presume that participants will receive a wide range of total crystalloid volumes and that the more fluid patients receive, the more significant difference will be performed between the two groups. Also, we presume that the outcome may be related with participants’ initial renal function, which is defined according to KDIGO criteria [25] based on the fisrt creatinine or the urine output in the first 6, 12 or 24 hours after enrollment. Based on these anticipations, in the main secondary analysis, patients will be divided into several groups according to different crystalloid infusion volumes and distinct initial renal function, respectively. The proportion of patients experiencing the primary outcome will be compared between the same volume groups of saline and acetate Ringer’s solution respectively and between the same initial renal function groups, namely no AKI, AKI stage 1, AKI stage 2, and AKI stage 3, respectively. In this section, a logistic regression model with the primary outcome will be conducted to detect whether it differs significantly between saline and acetate Ringer’s solution infusion on renal outcome in the same volume group or the same initial renal function group, and then figure out whether the infused volume or initial renal function makes a difference.

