## Objectives

This trial is the first to focus on septic patients and verify if acetate Ringer’s solution is superior to saline, especially in patients with septic AKI. It is aimed to provide credible and evident data and clarify if (1) there is a significant difference in the overall outcome between acetate Ringer’s solution and saline in septic patients, (2) the effect is dependent on the baseline renal function, and (3) there is a dose-response effect by subgroup analysis.

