### Study treatments

The intervention of treatment lies in fluid management. To exclude the possible difference caused by different balanced crystalloid solution, acetate Ringer’s solution is chosen for balanced crystalloid infusion. After patient screening and grouping, participants will be assigned with acetate Ringer’s solution or saline for intravenous infusion accordingly. The volume, infusion rate, and additive content (e.g., potassium chloride) of the fluid will be determined by responsible clinicians. The intervention will last for 5 days after patients’ enrolment. Other solutions are permitted to be used as carrier fluids for the infusion of any drug on the occasion when neither acetate Ringer’s solution nor saline is considered compatible. Medication use except fluids will not be restricted in the study.

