### Study fluid distribution and logistics

Acetate Ringer's soution and saline administered in this trial both have different volume sizes of 250 ml and 500 ml. Components of these two crystalloids are presented (Table 2). The study is an open-label study; thus, the exact solution used is known to investigators, clinicians, and patients. Since the study is non-blind and two fluids used in this study have already been widely applied in the daily care of patients in the above ICUs, there are no problems of logistics.

**Table 2 Tab2:** Components of two crystalloids administered in the trial

Components (mmol/L)	Acetate Ringer’s solution	0.9% saline
Na	140	154
K	4	-
Mg	1	-
Ca	1.5	-
Cl	115	154
Glucose (%)	1	-
Buffer system	Acetate 25	-
Osmotic concentration (mOsmol/kg)	304	286

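### Dose-response is tested within groups of fluid volume received after assignment, and effect modification is read from stratum-by-stratum significance

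*Protocol article*

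**What the plan says.** All references are to the protocol article.

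- **Objectives.** After the overall comparison, the trial asks whether "the effect is dependent on the baseline renal function, and (3) there is a dose-response effect by subgroup analysis".
- **Main secondary analysis.** The expectation is that "the more fluid patients receive, the more significant difference will be performed between the two groups". On volume, "The proportion of patients experiencing the primary outcome will be compared between the same volume groups of saline and acetate" Ringer's solution; the same is done within four groups by initial renal function (no AKI and AKI stages 1 to 3). A logistic model looks for a significant difference between fluids within each group, "and then figure out whether the infused volume or initial renal function makes a difference".
- **Definition of initial renal function.** The same section stages it "based on the fisrt creatinine or the urine output in the first 6, 12 or 24 hours after enrollment". Additional secondary analysis uses AKI status on the enrolment day, with other categories: no AKI, AKI, and chronic kidney disease without regular renal replacement therapy (RRT).
- **How volume arises.** Under Study treatments, "The volume, infusion rate, and additive content (e.g., potassium chloride) of the fluid will be determined by responsible clinicians", and "The intervention will last for 5 days after patients’ enrolment". Under Study fluid distribution and logistics, "the exact solution used is known to investigators, clinicians, and patients".
- **Other subgroups.** Additional secondary analysis also lists RRT receipt and days, ventilation days and maximum vasopressor dose.

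**The concern.** Received volume is a consequence of what happens after assignment. Clinicians who know the fluid choose it in response to the patient's course, and it stops accruing at death, which is itself part of MAKE28. If fluid type changes how much is given, or how closely volume follows severity, then saline and acetate patients in the same volume group are no longer alike at baseline. A difference inside the group may then reflect selection.

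Separately, finding significance in one group and not in another does not show that the effect differs between them. In small strata this pattern is common when the effect is uniform, and it also arises when there is no effect.

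These analyses carry the second and third objectives. The Summary/discussion presents volume and baseline renal function as the trial's particular contribution and expects the results to inform fluid guidance.

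**Working it through.** The plan gives no figure for these analyses. Its target of 312 was sized for the overall comparison, and nothing below rests on that calculation.

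**1. Timing of each stratifying variable**

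| Variable | When fixed | Status |
|---|---|---|
| Received volume | Over 5 days, open label | Post-assignment |
| First creatinine; enrolment-day AKI status | At or near enrolment | Close to baseline |
| Urine output at 6, 12 or 24 h | After enrolment | Post-assignment |
| RRT receipt and days, ventilation days, maximum vasopressor dose | During follow-up | Post-assignment |

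**2. Possible bias within volume groups, with no true fluid effect**

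From the document: MAKE28 risk of about 35% (Sample size and statistical power). Assumed: severity S ~ N(0,1); logit P(MAKE28) = -0.74 + S, which gives 35% overall; volume in litres = 5 + 1.5·S + δ·(saline) + N(0, 1.5²), so the SD of volume is √(1.5² + 1.5²) = 2.1 L. Two million simulated patients were split into tertiles of received volume. The table gives saline minus acetate in percentage points.

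| δ (saline volume minus acetate) | Low | Middle | High |
|---|---|---|---|
| 0 L | about 0 | about 0 | about 0 |
| -0.5 L | +2.0 | +3.0 | +2.6 |
| -1.0 L | +3.8 | +6.1 | +5.2 |
| +0.5 L | -1.7 | -3.1 | -2.5 |
| +1.0 L | -3.9 | -6.3 | -5.3 |

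The bias is real under these assumptions, takes the opposite sign to δ, and is not monotone across tertiles. A false gradient (-4.4, -0.7, +5.0) appeared only under a further assumption, that volume tracks severity less closely in the acetate arm.

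**3. Reading significance stratum by stratum**

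Inputs: 156 per arm and 20% withdrawal (Sample size and statistical power); four renal groups (Main secondary analysis); P < 0.05 (Statistical analysis). Assumed: equal strata and independent tests. Patients per arm per stratum: 156/4 = 39, or 156 × 0.8/4 = 31.2 after withdrawal.

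- *No effect:* P(at least one significant) = 1 - 0.95⁴ = 18.5%. Simulation gives 18% to 19%.
- *Uniform effect of 10 points, 35% v 25% (assumed):* power in one stratum = Φ{[0.10 - 1.96·√(2·0.30·0.70/n)] / √[(0.35·0.65 + 0.25·0.75)/n]}, which is 0.158 at n = 39 and 0.135 at n = 31.2.
- P(some but not all significant) = 1 - p⁴ - (1-p)⁴. At n = 39 this is 1 - 0.0006 - 0.5026 = 49.7%. At n = 31.2 it is 1 - 0.0003 - 0.5598 = 44.0%. Simulation gives 52% (n = 39) and 44% (n = 31).
- *Uniform effect of 5 points:* 25% (n = 31) to 28% (n = 39) by simulation.
- *Comparison:* with 250 evaluable patients, a test of heterogeneity across strata rejected in about 6% of trials when the effect was uniform or absent.

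**4. The RRT subgroup**

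Prior RRT is an exclusion (Participant patients), and new RRT is a component of MAKE28 (Study outcomes). Every patient with RRT in the 28-day window therefore has the event. For MAKE28, the RRT-yes group has 100% events in both arms by definition, so nothing can be compared there.

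**The case against.** Four points can fairly be made for the plan.

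- **The volume bias is hypothetical.** It needs fluid type to affect the volume given or how volume tracks severity, and the document has no data on either. This stands as to size and sign. It does not rescue the analysis, because nothing in an open-label design with discretionary volume secures the condition under which the bias vanishes.
- **The article is condensed, and an interaction term is commonly left to the analysis plan.** Absence of the term alone would be no finding. But the text describes a route: test within each group, then conclude about volume or renal function. Followed as written, that is the error worked through above.
- **Renal function is largely a baseline variable.** This stands. First creatinine and enrolment-day status are usable; only the urine-output route runs into the treatment period.
- **RRT receipt tests neither objective.** This also stands. It is only an additional subgroup, is absent from the list of pre-specified subgroups in Study outcomes, and is degenerate only when the outcome is MAKE28.

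A reader might infer that both objectives are beyond answer, that the plan will produce a dose-response where none exists, or that the AKI outcome must be redefined. The document supports none of these. The renal objective is answerable once its baseline is fixed. The simple volume-shift model gives a false difference but no monotone gradient. AKI is not a component of MAKE28, so its definition does not enter these analyses.

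**Conclusion.** The point holds in this form. Objective 3 cannot be answered causally by comparing arms within received-volume groups. The size and sign of the bias are unknown: about 0 if volume is independent of fluid, and about 2 to 6 points in either direction under assumed arm differences of 0.5 to 1 L.

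For both objectives, stratum-wise significance is an unreliable guide to effect modification: about 19% false signals with no effect, and about 44% to 52% mixed results under a uniform 10-point effect. Those figures assume four equal strata with 31 to 39 patients per arm in each, and the mixed-result figure falls to 25% to 28% at 5 points. It would be too much to say that a uniform effect will usually look mixed, since that depends on an effect size the plan does not give.

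Objective 2 remains answerable, subject to one definition of initial renal function. The post-assignment subgroups in Additional secondary analysis are a separate and lesser fault. The primary intention-to-treat comparison is not affected.

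**What to change.** 1. Test each question with one treatment-by-modifier interaction in the primary model. Report stratum estimates with confidence intervals and not stratum-wise P values.
2. Label comparisons by received volume as descriptive and non-causal. Test the volume question with a baseline variable, for example volume predicted from severity, shock status and pre-ICU fluid. Step 1 alone does not repair received-volume strata.
3. Reconcile Main secondary analysis and Additional secondary analysis to one AKI stage from data at or before enrolment: first creatinine, and urine output only where recorded before study fluid began.
4. Drop RRT receipt and days, ventilation days and maximum vasopressor dose as subgroups. Use ventilation and vasopressor status at enrolment.

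The cost is mainly analysis wording and some programming. The reading by actual litres becomes descriptive. Interaction tests will have low power at 312 patients. AKI staging may rest mainly on creatinine, because recruitment began in March 2019 and urine output from before study fluid may not have been recorded. No change to the AKI outcome definition is needed for this defect.
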